# STATISTICS

## Endpoint analysis will be carried out after all participants have completed visit 7 (13 month blood sample). An additional analysis will be carried out after the final follow-up visit at 24 months of age (visit 8). An interim analysis will be carried out after all participants have completed visit 4 (5 month blood sample).

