***Statistical Analysis***

The analysis of the outcome variables will be performed on the intention–to-treat (ITT) population for the reduced dose MenC objectives and the completers population for the alternating limb objectives. A subject is included in the ITT population if they have at least one dose and at least one post-baseline assessment, and in the completers population if they receive all doses of vaccine and have all planned assessments.

An analysis of variance will be performed when the outcome variable is continuous. The model will contain the terms dose group (4 levels) and alternating limb group (2 levels). A term for centre will be included in the model. The results of a comparison between any two levels of a factor will be reported as a treatment effect with 95% confidence interval.

For the analysis of variables relating only to 0 dose control group the term relating to dose group will be omitted.

The following outcomes will be analysed (comparisons of interest are listed):

1. MenC rSBA GMT response variable assessed 28 days after the Hib-MenC 12 month booster dose
   1. Single dose MenC-CRM197 Group vs. Two dose MenC Group
   2. Single dose MenC-CRM197 Group vs. 0 dose control Group
   3. Single dose MenC-TT Group vs 0 dose control Group
   4. Two dose MenC Group vs. 0 dose control Group
   5. Single Dose MenC-CRM197 Group vs Single Dose MenC-TT Group
2. MenC rSBA GMT response variable assessed 6 days after the Hib-MenC 12 month booster dose
   1. Single dose MenC-CRM197 Group vs. Two dose MenC Group
   2. Single dose MenC-CRM197 Group vs. 0 dose control Group
   3. Single dose MenC-TT Group vs 0 dose control Group
   4. Two dose MenC Group vs. 0 dose control Group
   5. Single dose MenC-CRM197 Group vs Single dose MenC-TT Group

3. MenC rSBA GMT response variable assessed 12 months after the Hib-MenC 12 month booster dose

1. Single dose MenC-CRM197 Group vs. Two dose MenC Group
2. Single dose MenC-CRM197 Group vs. 0 dose control Group
3. Single dose MenC-TT Group vs 0 dose control Group
4. Two dose MenC Group vs. 0 dose control Group
5. Single dose MenC-CRM197 Group vs Single dose MenC-TT Group
6. MenC rSBA GMT response variable (persistence) assessed at 12 months of age
   1. Single dose MenC-CRM197 Group vs. Two dose MenC Group
   2. Single dose MenC-CRM197 Group vs. 0 dose control Group
   3. Single dose MenC-TT Group vs 0 dose control Group
   4. Two dose MenC Group vs. 0 dose control Group

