## 9.7 Inclusion in Analysis

The immunogenicity analysis will be performed on both an intention to treat (ITT) population (all participants completing their designated primary and booster stage immunisation courses, and providing blood samples at the timepoint being analysed) and on a completers protocol (CP) population (all participants in the intention to treat analysis completing the study without any significant protocol deviations).

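### Sections 9.1 and 9.7 define ITT and completers differently and disagree on which set the MenC analysis uses; read literally, completers cannot be determined at the Visit 7 endpoint analysis

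*Protocol*

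**What the plan says.** **ITT.** Section 9.1, under Statistical Analysis, reads: "A subject is included in the ITT population if they have at least one dose and at least one post-baseline assessment". Section 9.7 describes ITT as "all participants completing their designated primary and booster stage immunisation courses, and providing blood samples at the timepoint being analysed".

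**Completers.** Section 9.1 counts a child "in the completers population if they receive all doses of vaccine and have all planned assessments". Section 9.7 describes CP as "all participants in the intention to treat analysis completing the study without any significant protocol deviations".

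**Which set is used.** Section 9.1 takes the ITT "population for the reduced dose MenC objectives and the completers population for the alternating limb objectives". Section 9.7 states: "The immunogenicity analysis will be performed on both an intention to treat (ITT) population", and adds the CP population.

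**When.** The opening of section 9 reads: "Endpoint analysis will be carried out after all participants have completed visit 7 (13 month blood sample"). It places an interim analysis after Visit 4 and a further analysis after Visit 8, the last visit in Appendix B.

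**Related places.**
- Section 6.3.4 says the elimination criteria may affect CP evaluability, without making this a fixed rule.
- Section 7.5 excludes some children from an according-to-protocol (ATP) analysis that section 9 never defines.
- Section 6.6 keeps samples already collected from withdrawn children in the analysis.
- Section 9.5 makes no allowance for missing data.

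**The concern.** The primary question is non-inferiority of one priming dose to two, and the protocol gives two answers to who is counted. The section 9.7 set called ITT is selected on what happened after randomisation (finishing the course), so it is not ITT in substance. The section 9.1 set keeps children whatever they received.

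The children on whom the sets differ are not neutral. A Two Dose child without the 4-month dose has had the MenC priming of a Single Dose child. If one dose is truly weaker, keeping that child in the Two Dose arm narrows the difference and helps the non-inferiority claim; dropping that child gives up the randomised comparison. Either choice can be defended, but a choice still open when the data are seen cannot.

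The completers rule raises a second matter. If membership depends on Visit 8, it is unknown for many children when the endpoint analysis is due. The rule also removes sound 5-, 12- and 13-month results because a later bleed was missed.

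**Working it through.** **1. The plan's own figure.** Inputs from sections 9.2 and 9.3: margin M = 0.35 log10, SD = 0.9, true difference 0, one-sided alpha 0.025, power 90%.

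n per group = 2 × (1.960 + 1.282)² × 0.9² / 0.35² = 139 after rounding up. The protocol states 140. With the unrounded margin 0.347 the result is 142. Drop-out: 140 / (1 − 0.125) = 160, as stated. The sample size is sound; the issue is who counts towards the 140.

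**2. Membership, case by case.**

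| Child | ITT in 9.1 | ITT in 9.7 | Effect |
| --- | --- | --- | --- |
| Two Dose, 4-month MenC dose missed, booster given, bled at Visit 7 | in | out | enters the primary model under 9.1 only |
| Full course, bled at Visit 4, no Visit 7 sample | in | out at Visit 7 | none: no titre, and section 9.5 makes no allowance for it |
| Withdrawn before the booster, bled at Visit 4 | in | out | 5-month result kept by 9.1 and 6.6, dropped by 9.7 |

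For the primary endpoint the sets therefore differ only for children with a Visit 7 titre and an incomplete course.

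**3. Timing.**

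| Analysis | Run after | What the set needs | Can membership be settled? |
| --- | --- | --- | --- |
| Interim, ITT as in 9.7 | Visit 4 | 12-month booster | not for children still short of 12 months |
| Endpoint, completers as in 9.1 | Visit 7 | every planned assessment, through Visit 8 | not for children still short of Visit 8 |
| Endpoint, CP as in 9.7 | Visit 7 | study completed | not for children still short of Visit 8 |

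Visit 7 falls 28 to 42 days after the booster and Visit 8 falls 11 to 12 months after it (Appendix C), so the gap is about ten months.

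**4. Which set decides.** Section 9.1 names ITT for the MenC objectives and completers for the limb objectives. Section 9.7 names both sets for immunogenicity as a whole. Neither says whether one set governs or both must succeed.

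**5. What a smaller set costs.** Power = Φ(0.35 / (0.9 × √(2/n)) − 1.960), with the true difference 0.

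| Evaluable per group | Power |
| --- | --- |
| 160 | 93.5% |
| 140 | 90.2% |
| 128 | 87.5% |
| 120 | 85.4% |
| 100 | 78.5% |

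Only 160 and 140 come from the protocol. The other sizes are assumed, because no expected exclusion rate from CP is given. If non-inferiority has to be shown in both sets, power cannot exceed that of the smaller set.

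**The case against.** Four replies deserve weight.

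- **The protocol does include a CP analysis.** A reader of section 9.1 might infer that non-inferiority rests on ITT alone. That is true of 9.1 but not of the protocol, because 9.7 adds CP. What stands is the contradiction and the missing decision rule.
- **The gap between the ITT sets is narrow.** This is correct. A child without a Visit 7 titre contributes nothing under either definition, and no count is given of children with a titre but an incomplete course.
- **The completers timing does not reach the primary test as 9.1 writes it,** since 9.1 uses completers for the limb comparison, which section 9.2 calls pilot data. Planned assessments could also mean those planned to date. That reading would rescue 9.1, though the text does not say it. It does not rescue 9.7, which asks for completion of the study and applies CP to immunogenicity generally.
- **A SAP may settle this.** It might, but the point is two conflicting statements in the protocol, not detail left for later.

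A reader might also try to size the problem with the 12.5% in section 9.2, as a rate of missed 4-month doses or of failed bleeds at each visit. The documents support neither use. It is a drop-out allowance. A child lost before Visit 7 gives no titre and so dilutes nothing. Bleeds may be attempted twice and repeated at a second visit.

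**Conclusion.** The contradiction is real, and it concerns the set on which the primary claim is tested. ITT has two memberships, completers has two definitions that both run literally to Visit 8, and the rule for deciding non-inferiority differs between sections 9.1 and 9.7. These conclusions follow from the text and need no assumed rates.

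The effect on the primary estimate cannot be sized from the documents. Its direction is conditional: with the section 9.1 set, missed second doses favour non-inferiority only if one dose is truly inferior to two. A reader might conclude that the primary result will turn on which section is followed. That is possible but not shown.

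Nor do the documents establish that ITT must come first for the limb comparison. A set based on vaccines given as allocated is defensible for a pilot question about injection limb, provided it is defined per visit.

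This should be fixed before the endpoint analysis. It does not undermine the design or the sample size.

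**What to change.** - **ITT:** use one definition in 9.1 and 9.7, namely all randomised children, analysed as randomised, with a result at the visit analysed.
- **CP:** define it per visit. All study vaccines due up to that visit were given as allocated, no elimination criterion was met, and there is a valid sample at that visit. This removes the dependence on Visit 8 and keeps sound earlier results. Align section 6.3.4 with it, and replace the ATP label in section 7.5.
- **Decision rule:** state in advance how ITT and CP decide the primary claim. At minimum, report in both sets whether the lower limit of the two-sided 95% interval for Single Dose minus Two Dose lies above -0.35, and require consistent conclusions.
- **Limb comparison:** the sponsor may choose the primary set, if it is defined per visit.

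The cost is protocol and SAP wording and at most one further run of the primary model. The downside is some loss of power if CP falls below 140 per group, on the scale tabulated above.

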This study would also provide the opportunity to investigate whether the immunogenicity of the Hib, tetanus and pneumococcal components, within the routinely recommended vaccines (Pediacel and Prevenar-13), that are administered concurrently with the MenC vaccine would be affected if sequential doses are administered within the same limb or in the alternating limb. Protection against vaccine preventable diseases is dependent on the generation of sustained and functional disease-specific antibody concentrations or a timely ‘secondary’ antibody response on exposure to the relevant disease which in turn are dependent on the generation of mature B cells in lymph nodes draining the site of vaccination. After priming, a significant proportion of mature B cells remain within these nodes9, accompanied by retained antigen and memory CD4 T-cells that can aid antibody responses10. Memory B cells appear to preferentially home to lymph nodes that have been primed with their cognate antigen27. Sequential immunisations, as performed in clinical trials, may therefore be more effective if given into the same limb since vaccine antigens should reach more memory B and T-cells, resident in draining lymph nodes. Post licensure sequential doses of vaccines are not usually administered in the same limb, a practice that was shown to result in reduced response rates to an intradermal rabies vaccine28. No further studies have been performed to assess the effect that alternating limbs with sequential immunisations has on the immunogenicity of conjugate vaccines.

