***Single dose MenC-CRM197 Group n=160**

MenC-CRM197 at 3 months

Visit 5

Visit 6**

Visit 7

Hib-MenC boost + PCV13 at 12 months

VP

VP

VP

VP

*Control group n=64

Visit 2

Visit 3

MMR

Visit 8

VP

*Single dose MenC-TT Group n=114 MenC-TT at 3 months

*Participants would be randomised to receive MenC-CRM197 at 3 and 4 months (Two Dose MenC Group), or a single dose at 3 months (Single Dose MenC-CRM197 Group) or a single dose of MenC-TT at 3 months (Single dose MenC-TT Group) or no priming doses (Control Group). All participants will receive the DTaP-IPV-Hib vaccine at 2, 3 and 4 months and the PCV13 at 2 and 4 months according to the UK immunisation schedule. All participants would be boosted with the Hib-MenC vaccine and the booster dose of PCV13 at 12 months and will receive the MMR vaccine at 13 months.

Venepuncture (VP), taking 5 ml of blood, will be performed at 5 months (Visit 4), and taking 7.5ml of blood will be performed at 12 months (Visit 5), 12 months+6 days (Visit 6), at 13 months (Visit 7) and at 24 months (Visit 8). Two attempts may be made to obtain a blood sample at each visit, if the parent gives verbal consent at the time of the procedure for a second attempt. If no blood is obtained, a second visit may be made if the parent agrees to this.

** Visit 6 will be performed on all participants in the control group and a subset of 64 participants in the Two Dose MenC, Single Dose MenC-CRM197 and Single Dose MenC-TT groups (as determined by randomisation at enrolment, see section 6.4.4)

In addition, participants will be randomised at enrolment to receive PCV13 and DTaP-IPV-Hib in either consistent limbs (subgroup a) or alternating limbs (subgroup b) as follows

| **Subgroup a**  (Consistent limbs) | **Subgroup b**  (Alternating limbs) |
| --- | --- |
| DTaP-IPV-Hib in right leg at 2, 3 and 4 months  PCV13 in right leg at 2, 4and 12 months | DTaP-IPV-Hib in left leg at 2 months and in right leg at 3 and 4 months*  PCV13 in left leg at 2 months, right leg at 4 months and left arm at 12 months |

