14. the *S. pneumoniae* IgG GMC response variable for each of the thirteen serotypes separately, (persistence) at 12 months of age
    1. the consistent limb group vs. the alternating limb group

1. the *S. pneumoniae* IgG GMC response variable for each of the thirteen serotypes separately at 13 months of age after the PCV-13 booster dose
   1. the consistent limb group vs. the alternating limb group
2. 12. the *S. pneumoniae* IgG GMC response variable for each of the 13 serotypes separately at 24 months of age.
   1. the consistent limb group vs. the alternating limb group

1. the anti-PRP IgG GMC response variable at 5 months of age
   1. the consistent limb group vs. the alternating limb group
2. the anti-PRP IgG GMC response variable (persistence) at 12 months of age
   1. the consistent limb group vs. the alternating limb group

1. the anti-PRP IgG GMC response variable at 13 months of age, after the Hib-MenC booster dose
   1. the consistent limb group vs. the alternating limb group
2. the anti-PRP IgG GMC response variable at 24 months of age
   1. the consistent limb group vs. the alternating limb group
3. the anti-tetanus toxoid GMC response variable at 5 months of age ,
   1. the consistent limb group vs. the alternating limb group
4. the anti-tetanus toxoid GMC response variable (persistence) at 12 months of age
   1. the consistent limb group vs. the alternating limb group

1. the anti-tetanus toxoid GMC response variable at 13 months of age
   1. the consistent limb group vs. the alternating limb group
2. the anti-tetanus toxoid GMC response variable at 24 months of age
   1. the consistent limb group vs. the alternating limb group

The binary variables will be analysed using logistic regression. The model will contain the terms dose group (4 levels), and alternating limb group (2 levels). There will also be a term for centre. The results of a comparison between two levels of a factor will be reported as an odds ratio and as a risk difference, with 95% confidence intervals.

For the analysis of variables relating only to 0 dose control group the term for dose group will be omitted.

The following binary outcomes will be analysed:

1. percentage of infants with MenC rSBA ≥ 1:8 and ≥ 1:128 assessed 6 days after the 12 month Hib-MenC booster
   1. Single dose MenC-CRM197 Group vs. Two dose MenC Group
   2. Single dose MenC-CRM197 Group vs. 0 dose control Group
   3. Single dose MenC-TT Group vs 0 dose control Group

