# APPendix a: study flow CharT

| **Details of vaccine administration for each treatment group** | | | **Visit 1** | **Visit 2** | **Visit 3** | **Visit 4** | **Visit 5** | **Visit 6*** | **Visit 7** | **Visit 8** |
| --- | --- | --- | --- | --- | --- | --- | --- | --- | --- | --- |
|  |  |  | **Blood** | **Blood** | **Blood** | **Blood** | **Blood** |
| **Two Dose MenC Group**  **(2 doses MenC-CRM197)**  **Group 2** | **a** | Right leg | DTaP-IPV-Hib  PCV13 | DTaP-IPV-Hib | DTaP-IPV-Hib  PCV13 |  | PCV13 |  | MMR |  |
| Left leg |  | *MenC****-CRM197*** | *MenC****-CRM197*** |  | Hib-MenC |  |  |
| **b** | Right leg |  | DTaP-IPV-Hib | DTaP-IPV-Hib  PCV13 |  |  |  | MMR |  |
| Left leg/ arm | DTaP-IPV-Hib  PCV13 | *MenC***-*CRM197*** | *MenC****-CRM197*** |  | Hib-MenC (leg), PCV13 (arm) |  |  |
| **Single Dose MenC-CRM197 Group**  **(1 dose MenC-CRM197)**  **Group 1** | **a** | Right leg | DTaP-IPV-Hib  PCV13 | DTaP-IPV-Hib | DTaP-IPV-Hib  PCV13 |  | PCV13 |  | MMR |  |
| Left leg/ arm |  | *MenC***-*CRM197*** |  |  | Hib-MenC |  |  |
| **b** | Right leg |  | DTaP-IPV-Hib | DTaP-IPV-Hib  PCV13 |  |  |  | MMR |  |
| Left leg/ arm | DTaP-IPV-Hib  PCV13 | *MenC****-CRM197*** |  |  | Hib-MenC (leg) PCV13 (arm) |  |  |
| **Control Group**  **(0 dose MenC priming)**  **Group 3** | **a** | Right leg | DTaP-IPV-Hib  PCV13 | DTaP-IPV-Hib | DTaP-IPV-Hib  PCV13 |  | PCV13 |  | MMR |  |
| Left leg/ arm |  |  |  |  | Hib-MenC |  |  |
| **b** | Right leg |  | DTaP-IPV-Hib | DTaP-IPV-Hib  PCV13 |  |  |  | MMR |  |
| Left leg/ arm | DTaP-IPV-Hib  PCV13 |  |  |  | Hib-MenC (leg) PCV13 (arm) |  |  |
| **Single Dose MenC-TT Group**  **(1 dose MenC-TT)**  **Group 4** | **a** | Right leg | DTaP-IPV-Hib  PCV13 | DTaP-IPV-Hib | DTaP-IPV-Hib  PCV13 |  | PCV13 |  | MMR |  |
| Left leg/ arm |  | *MenC-TT* |  |  | Hib-MenC |  |  |
| **b** | Right leg |  | DTaP-IPV-Hib | DTaP-IPV-Hib  PCV13 |  |  |  | MMR |  |
| Left leg/ arm | DTaP-IPV-Hib  PCV13 | *MenC-TT* |  |  | Hib-MenC (leg) PCV13 (arm) |  |  |

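### After the 12-month Hib-MenC-TT booster, given on the left in both limb subgroups, the anti-PRP and anti-tetanus contrasts compare R,R,R,L with L,R,R,L and do not test same-limb against alternating-limb dosing

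*Protocol*

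**What the plan says.** The limb table in Protocol section 6.1 defines the two subgroups. For subgroup a it gives "DTaP-IPV-Hib in right leg at 2, 3 and 4 months"; for subgroup b, "DTaP-IPV-Hib in left leg at 2 months and in right leg at 3 and 4 months". The table follows PCV13 through to 12 months but gives no 12-month site for the Hib-containing booster.

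That site appears only in Appendix A, at Visit 5. In the left-side row of Group 2b the entry is "Hib-MenC (leg), PCV13 (arm"), and the other b rows say the same. In the a rows Hib-MenC also sits on the left. The row label is left leg in Group 2a and left leg/arm, with no further qualifier, in Groups 1a, 3a and 4a. The Group 4a row reads "Left leg/ arm | | *MenC-TT* | | | Hib-MenC", so MenC-TT was given on that side at Visit 2.

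The Synopsis names the booster as Hib-MenC-TT, and the Rationale identifies TT as tetanus toxoid. The booster therefore carries both antigens measured in the Hib and tetanus objectives.

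The Synopsis and sections 5.2, 6.2 and 9.1 carry the consistent-versus-alternating contrast for anti-PRP and anti-tetanus to 5, 12, 13 and 24 months. Section 9.1 lists "the anti-PRP IgG GMC response variable at 13 months of age, after the Hib-MenC booster dose" and "the anti-tetanus toxoid GMC response variable at 13 months of age", with the matching 24-month and threshold outcomes. Nothing in the Protocol remarks on the side used for the booster.

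**The concern.** The Rationale, under the alternating limb component, states the hypothesis. Sequential doses "may therefore be more effective if given into the same limb since vaccine antigens should reach more memory B and T-cells", because those cells reside in the draining nodes that were primed before. What matters at any dose is thus whether that side has already seen the antigen.

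At the booster, the subgroup called consistent receives Hib and tetanus antigen on the side opposite to every DTaP-IPV-Hib dose. The subgroup called alternating receives it on a side that had the antigen at 2 months. From 13 months on, neither subgroup is consistent for these antigens.

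The plan as written would report these results under the same heading as the 5- and 12-month ones. A null finding could be two opposing effects cancelling. A difference favouring subgroup b could agree with the draining-node hypothesis, yet look like evidence against it.

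**Working it through.** **Inputs.** Priming sides: section 6.1 limb table. Booster side and MenC-TT side: Appendix A, Visits 5 and 2. Group sizes 160, 160, 114 and 64: section 9.2. Limb allocation 1:1 within each dose group: section 6.4.4. The Protocol states no sample size or power for the limb component, so there is no figure of its own to reproduce.

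**Step 1: sequence of Hib/tetanus doses** (DTaP-IPV-Hib at 2, 3 and 4 months, Hib-MenC-TT at 12 months).

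| Subgroup | 2 mo | 3 mo | 4 mo | 12 mo |
| --- | --- | --- | --- | --- |
| a (consistent) | R | R | R | L |
| b (alternating) | L | R | R | L |

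The subgroups differ at one dose only, the first. The booster side does not vary with subgroup.

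**Step 2: planned children per limb subgroup.** 160/2 + 160/2 + 114/2 + 64/2 = 80 + 80 + 57 + 32 = 249 in each of a and b.

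**Step 3: had the boosted (left) side been primed?**

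| Antigen | Subgroup a | Subgroup b |
| --- | --- | --- |
| PRP | 0 of 249 | 249 of 249 (at 2 months) |
| Tetanus | 57 of 249 = 22.9% (Group 4a, MenC-TT at 3 months) | 249 of 249 |

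**Step 4: direction of the components.** On the log scale, write the post-booster contrast as (a − b) = priming component + booster-side component. Under the stated hypothesis the priming component is zero or positive, because a had three doses on one side and b had a split series. The booster-side component is zero or negative, because the booster reaches previously primed nodes in b but, for PRP, in no child of a. The Protocol gives no size for either, so the sign of the sum is not determined and zero is possible.

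**Step 5: count of affected comparisons.** GMCs: PRP and tetanus = 2. Thresholds: PRP 0.15, PRP 1.0 and tetanus 0.1 = 3. Times: 13 and 24 months = 2. Total (2 + 3) × 2 = 10.

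**Step 6: what is not affected.** The 5-month sample precedes the booster, and section 6.3.6 lists the 12-month blood sample before vaccination at Visit 5. For PCV13 the sequences are R,R,R in a and left leg, right leg, left arm in b, so its label holds at all four times.

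**The case against.** The strongest reply is that the label is literally true. The objectives and endpoints define consistent and alternating by DTaP-IPV-Hib, and that series is R,R,R in a and L,R,R in b whatever happens later. Limb is randomised 1:1 within each dose group and the booster goes on the same side in both subgroups, so the late comparisons are unbiased for the effect of priming-limb pattern. This stands. A reader might infer that the ten comparisons are invalid or wrongly labelled; the documents do not support that. What fails is the interpretation as same-limb against alternating-limb dosing.

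Three further limits also stand:

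- A reader might say that every subgroup a child is boosted in a never-primed left leg. For tetanus this is wrong in Group 4a. In Groups 1a, 3a and 4a the row label allows leg or arm, so left side is certain and leg only implied. A left arm would equally be a limb not used for DTaP-IPV-Hib.
- Renaming the late contrasts purely by booster side would hide the priming difference, which is the factor that was randomised.
- MenC-TT in Group 4 does not bias the limb contrast. It goes on the left in both 4a and 4b, limb is randomised within the group, and the section 9.1 model includes dose group. It may modify the effect, so dropping 114 of 498 children (22.9%) from the main tetanus analysis is a preference, not a correction.

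Section 9.2 also calls the limb data pilot, and no decision rule depends on them. That lowers the stakes, but pilot data still have to be described by the exposure that produced them.

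**Conclusion.** The point holds as a matter of interpretation. For anti-PRP and anti-tetanus, ten planned comparisons at 13 and 24 months contrast R,R,R,L with L,R,R,L. They are valid randomised comparisons of priming pattern followed by a left-side booster, but they cannot show whether same-limb dosing matters.

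A reader might go further and infer that the post-booster effect must run against the label. The documents do not support this: under the Rationale the two components oppose each other, their sizes are not given, and the net direction is open.

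The conclusion assumes that Appendix A records the sides actually planned, and it uses the Protocol's own draining-node rationale. The count of 249 per subgroup assumes an exact 1:1 split of the planned group sizes. The primary objective, the PCV13 comparisons and the 5- and 12-month PRP comparisons are untouched. For tetanus at 5 and 12 months one caveat remains: Group 4a had tetanus toxoid on both sides before the booster.

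**What to change.** Reconcile sections 5.2, 6.2 and 9.1, and the matching Synopsis entries, with Appendix A:

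1. State the side of the 12-month Hib-MenC dose beside the limb table in section 6.1, as Appendix A already has it.
2. Limit the same-limb versus alternating-limb conclusion for anti-PRP and anti-tetanus to 5 and 12 months.
3. Describe the 13- and 24-month anti-PRP and anti-tetanus contrasts by their full sequence, R,R,R,L against L,R,R,L, and note that priming pattern and booster-side history are combined in them.
4. Optionally, add a sensitivity analysis of tetanus without Group 4.

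PCV13 keeps its label. No change to vaccination sites is proposed and no further data are needed. The cost is a wording change and a narrower claim for Hib and tetanus.
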